### Relevant Concomitant Care Permitted or Prohibited During the Trial

Adherence to interventions is crucial for scientific validity and participant well-being. The following strategies will be implemented to optimize adherence throughout the study: clear and comprehensive education during informed consent, and emphasizing the study’s purpose and the importance of adherence. Patients will be informed about the potential benefits, highlighting their contribution to advancing knowledge in lung cancer treatment. A multidisciplinary health care team, including surgeons, nurses, and support staff, will be involved in patient education and engagement. A collaborative approach ensures consistent information and support from various health care professionals. Treatment plans will be tailored to individual patient needs and preferences to enhance buy-in and motivation to adhere to the protocol. Patient-specific factors, such as lifestyle and cultural background, can improve adherence. Regular communication channels will be established between health care providers and participants to address concerns, provide ongoing support, and reinforce the importance of adherence. Telehealth or virtual platforms will be implemented for follow-up consultations to facilitate continuous communication. Patients will be included in decision-making to foster a sense of autonomy and ownership in the intervention process. Shared decision-making can enhance commitment and adherence to the chosen intervention. A robust monitoring system will be implemented to track participant progress and adherence. Timely feedback will be provided to participants on their progress. Acknowledgment of their contributions is considered positive reinforcement. Support programs, including psychological support and resources, will be offered to address the emotional and psychological aspects of the intervention. Support programs help patients to cope with challenges, fostering a positive attitude toward the intervention. Technologies, such as mobile apps and online platforms, will be adopted to provide educational materials, reminders, and real-time support. Technology can enhance engagement and facilitate communication between participants and health care providers. Flexibility will be offered in scheduling interventions to accommodate individual participant preferences and logistical considerations. Flexible scheduling can reduce barriers to adherence and increase overall participant satisfaction. Strategies will be implemented to maintain participant engagement, including newsletters, educational materials, and updates on study progress. This will ensure that participants feel connected and valued as contributors to the research endeavor.

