
### Provisions for Posttrial Care

The provisions for posttrial care in LUCENT are designed to ensure that participants receive appropriate medical attention and support even after their active involvement in the study has concluded. The posttrial care plan prioritizes the well-being of participants and addresses any ongoing medical needs that may arise. The key provisions for posttrial care include the following:

Continuity of standard medical care: Participants will continue to receive standard medical care for lung cancer as per established clinical guidelines, irrespective of their involvement in the study. The study team will facilitate the seamless transition of participants back to routine medical care provided by their health care providers.Access to study-related information: Participants will continue to have access to information related to the study, including summaries of study results, as they become available and appropriate for dissemination.Follow-up assessments: If any scheduled follow-up assessments or evaluations are part of the study protocol extending beyond the active trial period, participants will be informed about and encouraged to attend these follow-up appointments.AE monitoring: During the posttrial period, the study team will continue to monitor and address any AEs or complications related to the study interventions or procedures.Referral to specialists: If participants require specialized care or additional medical attention beyond the scope of the study, appropriate referrals to specialists will be facilitated.Communication and support: Participants will be provided with the contact information of the study team or a designated point of contact, allowing them to reach out with any questions or concerns about their participation or posttrial care.Emergency procedures: Clear procedures will be in place to manage any emergent medical situations that participants may face after the conclusion of the trial, with appropriate guidance on seeking urgent medical attention. The posttrial care provisions emphasize the ethical responsibility of the study team to prioritize participant welfare beyond the active study period. By providing ongoing support, access to information, and coordination with standard medical care, the study aims to ensure a comprehensive and ethical approach to the well-being of participants even after their active involvement in the observational study has ended.

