### Assignment of Interventions: Blinding

The blinding approach is as follows:

Participants: Owing to the nature of the surgical intervention, participants and those directly involved in their care can access the assigned intervention. It is challenging to blind participants and health care providers involved in surgical procedures.Care providers: Surgeons, health care providers, and clinical care teams responsible for delivering the interventions will not be blinded. Their awareness of the assigned surgical approach is essential for providing appropriate care.Outcome assessors: Outcome assessors will be blinded to the assigned interventions, particularly those collecting objective clinical data and endpoints. This includes individuals responsible for assessing recurrence rates, overall survival, and disease-free survival.Data analysts: Data analysts involved in the statistical analysis of study outcomes will be blinded to the assigned interventions. Blinding at this stage helps ensure unbiased data interpretation.Statistical team: The statistical team responsible for analyzing and interpreting the study results will conduct blinded analyses to prevent potential bias in reporting.Data monitors and auditors: To maintain objectivity, data and external auditors may also be blinded to treatment assignments during monitoring and auditing activities.

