### Data Collection and Management

The plans for the assessment and collection of outcomes are as follows:

Longitudinal clinical outcomes: Regarding assessment, long-term clinical outcomes, including recurrence rates, overall survival, and disease-free survival, will be assessed through regular follow-up visits and medical records review. Regarding collection, outcome assessors will collect data during scheduled follow-up visits, and data entry personnel will ensure accurate and timely recording in the study database.PROs: Regarding assessment, patient-reported well-being and quality of life outcomes will be assessed using online questionnaires. Regarding collection, participants will be provided access to secure online questionnaire-completion platforms. Data will be automatically recorded in the study database.Health care resource utilization: Regarding assessment, health care resource utilization, including hospital stay and postoperative care, will be assessed through medical records and billing data. Regarding collection, data collection personnel will extract relevant information from medical records, and billing data will be obtained and recorded for economic analyses.Treatment decision patterns: Regarding assessment, patterns in treatment decisions, considering tumor characteristics and patient preferences, will be assessed through medical records and clinician interviews. Regarding collection, data collection personnel will document treatment decisions in the study database based on comprehensive reviews of medical records.Economic and psychosocial impact: Regarding assessment, economic and psychosocial impact assessments will be conducted through standardized tools and interviews. Regarding collection, trained personnel will administer economic and psychosocial assessments, and the results will be recorded in the study database.AEs and complications: Regarding assessment, continuous monitoring and medical records review will assess AEs and complications. Regarding collection, data collection personnel and safety monitoring teams will document AEs and complications in the study database.Stratification factors: Regarding assessment, stratification factors, including tumor stage and patient demographics, will be assessed at baseline. Regarding collection, data collection personnel will collect baseline information during participant enrollment and document it in the study database.Data quality assurance: Regarding assessment, regular audits and validation checks will continuously monitor data quality. Regarding collection, data management personnel will conduct routine quality checks to ensure the accuracy and completeness of the collected data.Data security and confidentiality: Regarding assessment, data security and confidentiality measures will be assessed through regular reviews and audits. Regarding collection, data management personnel will implement encryption, access controls, and other security measures to protect participant information.Reporting and analysis: Regarding assessment, reporting and analysis plans will be periodically reviewed and updated as needed. Regarding collection, the statistical team will conduct blinded data analyses to generate reports for internal and external stakeholders.

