
The plans to promote participant retention and completion of follow-up are as follows:

Participant engagement initiatives: Implement a comprehensive plan to maintain ongoing communication and involvement. Regularly update participants on the study progress, key findings, and importance of their continued participation.Clear communication of study benefits: Communicate the potential benefits of the study to participants. Emphasize the contribution of their data in advancing scientific knowledge and improving lung cancer treatment strategies.Educational materials: Develop and distribute educational materials explaining the importance of follow-up assessments. Provide resources that enhance participants’ understanding of the study’s objectives and their role in contributing to research.Participant reminders: Implement a system of reminders for upcoming follow-up visits, assessments, and questionnaire completions. Use multiple communication channels, including emails, phone calls, and text messages, to ensure participants are aware of and prepared for scheduled activities.Flexible follow-up options: Offer flexible options for follow-up assessments, including virtual visits or alternative locations. Accommodate participant preferences to reduce barriers to attendance.Incentives for follow-up: Provide reasonable incentives for participants to complete follow-up assessments. Ensure that incentives comply with ethical guidelines and do not compromise the voluntary nature of participation.Dedicated study coordinator: Study coordinators will be a consistent point of contact, addressing participant queries and concerns.Continuous feedback loop: Establish a constant loop by soliciting participant feedback on their experiences.

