#### Interim Analyses

Interim analyses will be conducted at predetermined intervals to assess the study’s safety, efficacy, and futility. The analyses will be planned to coincide with critical milestones, such as the completion of a specific percentage of follow-up assessments or the occurrence of a predefined number of events. An independent data monitoring committee will be established to oversee interim analyses. The data monitoring committee will consist of experts in the field, statisticians, and clinicians who are not directly involved in the day-to-day conduct of the study. The data monitoring committee will have exclusive access to interim results. Unblinded provisional data will be shared with the data monitoring committee for their assessment of safety, efficacy, and overall study progress.

Clear stopping guidelines will be established in advance, outlining the criteria for stopping the trial. Controlling guidelines will include considerations for both safety and efficacy, with predefined thresholds for statistical significance. The trial may be stopped for the following reasons:

Efficacy: If interim analyses demonstrate overwhelming evidence of benefit, meeting predetermined criteria for early success.Safety: If there is a significant safety concern, meeting predefined criteria for harm.Futility: If interim analyses indicate that the study is unlikely to achieve its primary objectives.

The principal investigator and the steering committee will take the final decision to terminate the trial. The steering committee, comprising key study investigators, will consider the data monitoring committee’s recommendations and ultimately take a decision.

A clear communication plan will be in place to ensure timely and transparent reporting of interim results to relevant stakeholders. Communication channels will be predefined to facilitate the efficient dissemination of information. Any decision to stop the trial will be promptly reported to relevant ethical review boards and regulatory authorities. Transparent reporting ensures compliance with ethical standards and regulatory requirements.

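### Participants are to receive key findings regularly during follow-up, although interim results are reserved to the data monitoring committee; the access rules cannot all be followed

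*Protocol article*

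**What the plan says.** In Data Collection and Management, the list opened by "The plans to promote participant retention and completion of follow-up are as follows" includes the instruction "Regularly update participants on the study progress, key findings, and importance of their continued participation". The same section, under reporting and analysis, says that "the statistical team will conduct blinded data analyses to generate reports for internal and external stakeholders".

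The Interim Analyses section states "The data monitoring committee will have exclusive access to interim results". Further on it adds: "A clear communication plan will be in place to ensure timely and transparent reporting of interim results to relevant stakeholders". The stakeholders are not defined.

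Provisions for Posttrial Care gives participants continued access to study information once their own active involvement has ended, "including summaries of study results, as they become available and appropriate for dissemination".

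On blinding, the article accepts that "participants and those directly involved in their care can access the assigned intervention". Well-being and quality of life are collected by online self-report. The instrument is the EQ-5D-5L, and Table 1 lists health-related quality of life at baseline and at follow-up.

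**The concern.** The article gives several rules on who may see results before the study ends, and they are incompatible. One keeps interim results within the data monitoring committee, one sends them to stakeholders, and one tells participants key findings as a way of keeping them in the study. A site or newsletter writer who follows the retention plan breaks the committee rule.

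The conflict matters because the patient is the assessor for the patient-reported outcomes. Someone who knows which operation they had, and who is told how that approach or center is doing, may rate their own health differently afterwards. Blinding of outcome assessors and analysts gives no protection here. The adjustment described under Methods for Additional Analyses, for baseline characteristics and comorbidities, does not address an expectation created after baseline. The comparison exposed is a secondary one: the psychosocial impact of treatment pathways, for which the article's own example is minimally invasive surgery.

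**Working it through.** The article states no sample size, effect size or update frequency, so no bias can be calculated. The check sets the statements side by side and uses the study dates to see when they overlap.

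**1. Are the participant updates interim?** They are listed as a retention measure, so they run while follow-up is open. They are also to be regular, which does not fit a single release of final results. Any LUCENT finding they carry therefore comes before the final analysis.

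**2. Does another section narrow the term key findings?** No. Strategies to Improve Adherence to Interventions and the section on concomitant care both describe newsletters and updates on study progress only. The retention list is the place that adds findings. Posttrial care deals separately with summaries after a participant's active involvement.

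**3. Can the rules be followed together?**

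| Section | Who receives results | Timing |
|---|---|---|
| Interim Analyses, access rule | Monitoring committee only | Interim |
| Interim Analyses, communication plan | Undefined stakeholders | Interim |
| Data Collection and Management, retention | Participants | During follow-up |
| Data Collection and Management, reporting | Parties inside and outside the study | Not stated |
| Provisions for Posttrial Care | Participants who have finished | As available |

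The first row excludes the second and third. The fourth and fifth conflict with it whenever the release comes before the last participant's follow-up ends.

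**4. Do the dates make an overlap real?** Recruitment runs from January 01, 2024, to December 31, 2026, which is 3 × 12 = 36 months. Follow-up is at least 24 months.

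- A patient enrolled at the start is followed at least to January 2026. All 24 of those months fall inside the recruitment window, and 36 − 24 = 12 months of recruitment remain.
- A patient enrolled at the end is followed at least to the end of December 2028.
- Assuming follow-up stops at the 24-month minimum, the first participant finishes about 36 months before the last. During that time, summaries under posttrial care could reach some participants while others are still completing questionnaires.

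**5. Is there a path to an outcome?** For self-reported quality of life the path is direct: unblinded respondents, online self-report, and findings received between questionnaires. For later patients' choice of approach it has more steps. Updates go to people already enrolled, and Intervention Description bases the choice on tumor, patient and surgeon factors. On the other side, the article says "Patients will be included in decision-making to foster a sense of autonomy and ownership in the intervention process", names patient preference among the factors in treatment decisions, and uses advocacy groups to spread information during recruitment. None of these passages links preference to study results.

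**The case against.** The strongest reply is that harm depends on content the article never specifies. It does not say that participants will be shown findings by approach or by center. Pooled descriptive findings, such as the characteristics of those enrolled, would also count as key findings and would carry no comparative expectation. This stands: a reader might infer that comparative results will be sent to patients, but the text only leaves that open.

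Other stronger readings also go beyond the documents:

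- **Every patient is exposed before the last questionnaire.** An update reaches only those enrolled when it is issued. A patient enrolled in late December 2026 receives almost none of those sent during recruitment, and an update sent in 2026 could miss the earliest enrollees if their follow-up stopped at 24 months. The article gives neither an update frequency nor questionnaire times.
- **Later choices of approach and center case mix will shift.** No passage says that findings reach prospective patients or that patients change center because of them. Differences between early and late enrollees could also be examined by enrollment period.
- **The primary benchmarks are compromised.** The article's example is length of stay, and participant updates have little evident path to it.

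Two points of wording also deserve weight. Interim results might mean only the output of the formal interim analyses, leaving other findings free; but releasing findings from the same accumulating data would defeat the purpose of an exclusivity rule. The stakeholder reports come from blinded analyses and have no stated timing, so their conflict with the rule is weaker than that of the participant updates. Neither point removes the contradiction within Interim Analyses or between that section and the retention plan.

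**Conclusion.** The concern holds as a contradiction in the access rules, with a plausible but unquantified risk to secondary outcomes. The retention plan conflicts with the committee's sole access, and Interim Analyses conflicts with itself. The stakeholder reports and the posttrial summaries need to be brought into line.

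The risk of bias applies to patient-reported comparisons by approach or center. It rests on two assumptions: that the updates or reports contain findings by approach or center, and that participants' later answers respond to them. The documents establish neither, so no size can be given. An effect on later patients' choice is possible but indirect. The conclusion does not extend to the risk-adjusted benchmarks or to feedback given confidentially to centers, which is part of what a benchmarking registry is for. The conflict should still be corrected, because the change is cheap and the exposure avoidable.

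**What to change.** 1. **Data Collection and Management, retention list:** delete key findings. Limit updates during the study to progress, such as enrollment and questionnaire completion.
2. **Interim Analyses:** keep the committee's sole access. Limit interim reporting outside the committee to safety information that must be communicated and to any decision to stop, and say who the stakeholders are.
3. **Data Collection and Management, reporting and analysis, and Provisions for Posttrial Care:** state that outcome summaries by approach or center reach participants and external parties only after the last participant's follow-up. Posttrial care needs this explicitly, because early enrollees may finish while others are still being followed.
4. State that confidential benchmarking feedback to centers is not affected.

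The cost is a change of wording in these places and slightly less engaging participant updates. Reminders, coordinators, flexible visits, incentives and progress news all remain available for retention.

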### Data Management

The LUCENT data management process adheres to rigorous standards to ensure accuracy, integrity, and confidentiality. Standardized data collection forms will gather information consistently across all participating centers. Electronic data capture systems will be employed for efficient and accurate data entry. Regular checks and validations will be implemented to ensure the accuracy and completeness of the collected data. Data quality will be systematically monitored to identify and promptly address any discrepancies or errors. Secure and encrypted servers will be used to store electronic data. Access controls will be implemented to restrict unauthorized access to sensitive information. Stringent security measures, including encryption and secure authentication, will safeguard participant data. Compliance with relevant data protection regulations and guidelines will be maintained. Data will be shared according to appropriate ethical and legal frameworks if applicable. Access to data will be regulated to ensure privacy and confidentiality. A data monitoring committee will ensure that the study is conducted with the highest ethical and scientific standards.

